### Implementation of blind method

4.3

Due to the particularity of acupuncture clinical operation, this study will adopt a single-blind method, so only the efficacy evaluators and data statisticians will be blinded.

### Ethical review

4.4

Before recruiting patients, this study had passed the ethical approval of the medical ethics committee of Dongzhimen Hospital of Beijing University of Chinese medicine (approval number: DZMEC-KY-2020-06). The registration was completed in China Clinical Trial Registration Center (Registration Number: ChiCTR2000037444). All patients will be fully informed about the trail and given enough time to decide whether to participate in the study. All patients will be asked to sign an informed consent form if they agree to participate in the study.

## Treatment plan

5

### Acupuncture group

5.1

This group of patients will receive Western medicine treatment (each patient's specific medication should follow the advice of cardiovascular doctors), and will also receive acupuncture treatment at the same time. Record the type, dose, and frequency of drugs taken by each patient. The frequency of acupuncture will be once a day, 30 minutes each time, 5 times a week (2 days off), a total of 4 weeks.

#### Acupoint selection

5.1.1

Acupoint selection follows the semi standardized characteristics of acupuncture clinical research. Same main acupoints and reinforcing reducing manipulations will be used in this group, and the matching acupoints will be selected according to the principle of individualization.

Main acupoints: Taichong (LR 3-double); Baihui (DU 20); Taixi (KI 3-double); sanyinjiao (SP 6-double); Zusanli (ST 36-double).

Matching acupoints: headache: Fengchi (GB 20-double), Shuaigu (GB 20-double), Touwei (ST 8-double); insomnia: Sishencong (EX-HN), Benshen (GB 14-double), Shenting (DU 24), Shenmen (HT 7-double); excessive phlegm dampness syndrome: Yinlingquan (SP 9-double), Fenglong (ST 40-double); insufficiency of primordial QI: Qihai (RN 6), Guanyuan (RN 4).

#### Operation

5.1.2

It will be positioned according to the standard position of WHO in the Western Pacific Region.^[9]^ Acupuncture operation will be carried out according to the operation method of Acupuncture, a textbook of the 13th five-year plan of China.^[10]^ The manipulations will be carried out according to the operation standard of twirling reinforcing reducing manipulation which agreed by our research group. Andy brand acupuncture needle (0.30 × 40 mm × 100 pieces/box) will be used for acupuncture. Patients in supine or prone position, doctors choose acupoints according to the patient's personal situation. First of all, after local disinfection, then acupuncture to the appropriate depth. Make the acupoints De Qi (the patient's description are judged as “De Qi” by “acid, numbness, heaviness and distension”). Then, with the right hand as the needling hand, 1 minute reinforcing manipulation at Taichong (LR 3-double) and 1 minute reducing manipulation at Sanyinjiao (SP6-double) will be performed. Finally, the needles will be kept for 30 minutes.

Baihui (DU 20), Taixi (KI 3-double), Zusanli (ST 36-double), and other matching acupoints will only retain needles with no manipulations. Twirling reinforcing reducing manipulations are as follows. Twirling reducing manipulation: the thumb exerts the heavy force to twist backward, and the light force to forward return, twirling range is 270 to 360 °/time, 60 times/minute, continuous rotation for 1 minute, retention for 29 minutes, a total of 30 minutes. Twirling reinforcing manipulation: the thumb exerts the heavy force to twist forward, and the light force to backward return. The twisting range is 270 to 360 °/time, 60 times/minute, continuous rotation for 1 minute, retention for 29 minutes, a total of 30 minutes.

The acupuncture operators involved in this study are postgraduates majoring in acupuncture and moxibustion, and they have obtained the qualification certificate of licensed doctor for >2 years.

### Treatment plan of control group

5.2

The patients in the control group will be treated with antihypertensive drugs of western medicine, without changing the original western medicine treatment (the specific medication of each patient should follow the advice of cardiovascular specialist). And the patients will be instructed to take medicine regularly.

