### Experimental design

2.1

This is a single-center, single-blind, randomized, controlled, parallel group clinical trial. The selected patients will be divided into control group and experimental group according to the ratio of 1:1. The latter will receive acupuncture treatment for 4 weeks on the basis of the former. The data will be collected before acupuncture, after acupuncture, and 2 weeks after acupuncture. The process is shown in Figure 1.

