### Inclusion criteria

3.3

1.Age: 18 to 65 years, both male and female;2.Met the Western diagnostic criteria of essential hypertension. For patients without antihypertensive drugs, SBP: 140 to 179 mmHg and/or DBP: 90 to 109 mmHg. For patients with antihypertensive drugs, hypertension should be stabilized at a normal high value. The patients who took medicine used ≤2 antihypertensive drugs for >2 months.3.Confirmed TCM diagnosis of HLY in hypertension.4.Not receives acupuncture or Chinese herbal medicine treatment in recent 1 month.5.Good compliance with the observation and evaluation of researchers.6.Informed consent is signed by the patient himself or his immediate family members.

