#### Elimination criteria

3.5.1

1.The patients who do not complete the treatment according to the regulations or the data are incomplete, which affect the later evaluation.2.Noncompliant patients, those who withdraw from the research by themselves.3.Unauthorized use of drugs and treatment methods other than those specified in this protocol.4.During the trial, patients with serious adverse reactions or complications. The patients are intolerant of acupuncture therapy, or should not continue to receive treatment.5.Patients lost to follow-up.

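### The background antihypertensive drug rule is worded differently for the two arms and does not say what applies to patients who enter untreated

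*Protocol article*

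**What the plan says.** Section 2.1 defines the contrast between the control and experimental arms: "The latter will receive acupuncture treatment for 4 weeks on the basis of the former". Background treatment is then described separately for each arm.

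- Control arm (5.2): antihypertensive drugs "without changing the original western medicine treatment", followed in parentheses by a statement that each patient's medication follows specialist advice.
- Acupuncture arm (5.1): Western medicine, where "each patient's specific medication should follow the advice of cardiovascular doctors". There is no clause about leaving the existing treatment unchanged. The same paragraph adds: "Record the type, dose, and frequency of drugs taken by each patient".

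Eligibility (3.3) covers two kinds of patient. Treated patients must have used at most two drugs for more than two months. Untreated patients also qualify: "For patients without antihypertensive drugs, SBP: 140 to 179 mmHg and/or DBP: 90 to 109 mmHg".

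Under 4.3 only the efficacy evaluators and the statisticians are blinded. The primary outcome is 24-hour ambulatory blood pressure (6.1), and blood pressure is analysed by repeated-measures analysis of variance (9).

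**The concern.** In an add-on design the effect of the added treatment can be read from the arm difference only if everything else is handled alike. Antihypertensive drugs act directly on the primary outcome, so the drug rule matters more here than any other background rule.

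Two things are unclear as written. First, the clause that holds drugs constant stands in one arm's section and not in the other's. Second, it refers to a pre-existing treatment that some eligible patients do not have. Sites cannot tell from the text whether an untreated entrant starts a drug at entry, later or not at all, or whether the answer is the same in both arms.

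The doctors who advise on drugs are not listed as blinded, so their advice could differ by arm. A difference in drug starts or changes would then be mixed with the acupuncture effect.

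**Working it through.** **Step 1: the sections side by side.**

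| Question | 2.1 | 5.1 (acupuncture) | 5.2 (control) |
|---|---|---|---|
| Same background in both arms? | Implied | Not stated | Not stated |
| Existing drugs kept unchanged? | Not stated | Not stated | Yes |
| Medication follows specialist advice? | Not stated | Yes | Yes |
| Type, dose, frequency recorded? | Not stated | Yes, for each patient | Not stated |
| Rule for patients entering on no drug? | None | Receive Western medicine; start not defined | Receive drugs; existing treatment not defined |

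If 2.1 governs, the no-change clause belongs to both arms and 5.1 is incomplete. If 5.1 and 5.2 are each read alone, the rules differ and 2.1 is not met. On either reading, the untreated patients of 3.3 have nothing to which a no-change clause could apply.

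**Step 2: what an imbalance would do.** The plan states no figure on this point, so there is none to reproduce. The following is an illustration only.

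- From the document: 23 patients per arm before allowance for shedding and 56 recruited, i.e. 28 per arm (4.2); two-sided 5% tests (9).
- Assumed, not in the document: difference between arms in the share of patients starting or stepping up a drug, d = 10 to 30 percentage points; drug effect e = 5 to 10 mmHg; SD 10 to 15 mmHg; no true acupuncture effect.

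Bias b = d × e, from 0.10 × 5 = 0.5 mmHg to 0.30 × 10 = 3.0 mmHg. If the excess is in the acupuncture arm, the bias favours acupuncture. If it is in the control arm, the same size counts against acupuncture. If changes are equal, d = 0 and b = 0.

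SE = SD × √(2/n):
- SD 10, n = 23: 10 × √(2/23) = 2.95
- SD 10, n = 28: 10 × √(2/28) = 2.67
- SD 15, n = 23: 15 × √(2/23) = 4.42

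Chance of a significant result = P(|Z + b/SE| > 1.96), by normal approximation:

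| b (mmHg, either sign) | SD 10, n = 23 | SD 10, n = 28 | SD 15, n = 23 |
|---|---|---|---|
| 0.5 | 5.3% | 5.4% | 5.1% |
| 1 | 6.3% | 6.6% | 5.6% |
| 2 | 10.4% | 11.6% | 7.4% |
| 3 | 17.4% | 20.2% | 10.4% |

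The result runs from negligible to material, depending wholly on inputs the document does not give. Section 4.2 frames the sample size as noninferiority, but the article states no margin, so the two-sided test of section 9 is used here.

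**The case against.** The strongest reply is that one shared background is plainly intended. Section 2.1 puts acupuncture on top of the control treatment, 5.1 nowhere permits drug changes, and the specialist-advice wording is nearly the same in both arms. The no-change clause may simply have been written once. Even 5.2 can be read without contradiction: the regimen is whatever the specialist prescribed, and it is kept.

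Much of this stands, and it rules out several stronger readings that a reader might infer:

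- *Drugs are frozen in controls and free to change under acupuncture, so the error favours acupuncture.* Section 5.1 gives no such permission, and 5.2 also defers to the specialist. Changes could occur in either arm and the direction is open.
- *Untreated entrants become untreated controls.* Section 5.2 says controls are treated with antihypertensive drugs, and 4.1 calls the design a positive drug control. If untreated entrants start drugs equally in both arms, this creates no bias.
- *A drug change removes a control but not an acupuncture patient.* The elimination criterion in 3.5.1, "Unauthorized use of drugs and treatment methods other than those specified in this protocol", applies to all patients. A specialist-advised change is not clearly unauthorized in either arm. Section 3.5.2 also provides for an intention analysis and keeps those with more than half the course in the efficacy analysis.
- *Control-arm drugs go unrecorded.* The instruction sits under 5.1 but speaks of each patient, and section 8 sends all trial information to the CRF. This is a matter of placement.

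Detailed handling of drug changes in the analysis can also be left to an analysis plan that is not shown, so its absence is no error. What the reply does not remove is that the sections state the rule in two forms, and that neither form defines it for a group that 3.3 expressly admits.

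**Conclusion.** The point holds as an inconsistency between sections 2.1, 3.3, 5.1 and 5.2 that bears on the primary outcome. The text does not settle whether background drugs are held constant in both arms, and the existing treatment is undefined for drug-free entrants. With prescribers not listed as blinded, unequal drug starts or changes could bias the blood pressure comparison in either direction.

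The size cannot be determined from the documents. The 0.5 to 3 mmHg range and the rejection rates in the table rest entirely on the assumed imbalance, drug effect and SD; they show what an imbalance would do and do not predict that one will occur. The documents do not support a claim that the plan favours acupuncture or that its type I error is inflated by a known amount.

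**What to change.** Reconcile sections 2.1, 3.3, 5.1 and 5.2 so that one background-medication rule, in the same words, applies to both arms and expressly covers patients who enter untreated. What the rule requires is a clinical decision for the sponsor, and none is proposed here.

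Alongside it:

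- State that drug type, dose, frequency and every change during the trial are recorded in both arms, and report the changes by arm.
- Include drug status at entry as a covariate in the blood pressure analysis. Screening already establishes it, and simple randomization (4.1) does not guarantee that drug-free patients are split evenly. It adjusts for a baseline difference only; it does not correct for changes after randomization, which is why the common rule and the log are needed.

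The cost is protocol wording and one medication log used in both arms, with no extra visits or patients. It should be done before recruitment, because changes that are not logged cannot be compared between arms afterwards.

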## Efficacy index

6

### Main outcome

6.1

Ambulatory blood pressure monitoring: 24 hours ambulatory blood pressure is the “criterion standard” to evaluate the antihypertensive effect.^[11]^ In this study, the 24 hours ambulatory blood pressure monitor (DMS-ABP) made by American Tim will be used for data collection. Ambulatory blood pressure will be measured in patients’ nondominant arm to reduce the impact of activity on blood pressure measurement. The detection time of each patient should be >23 hours. At the same time, the effective reading is >70%. There are at least 20 daytime blood pressure readings and 6 nighttime blood pressure readings.

Ambulatory blood pressure monitoring will be evaluated in the first week (baseline period), the fifth week (after acupuncture period), and the seventh week (after follow-up period).

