**Methods::**

In this randomized controlled trial, we will recruit 56 hypertensive patients with hyperactivity of liver yang. Then the patients will be randomly divided into control group and experimental group. The control group will be treated with western medicine, and the experimental group will be treated with medicine combined with acupuncture. The intervention will last 4 weeks. The indices will be collected before acupuncture, after acupuncture, and 2 weeks after acupuncture. The primary outcome will be 24-hour ambulatory blood pressure. The secondary outcomes will be clinic blood pressure, anxiety and depression score, and the syndrome score of hyperactivity of liver yang. The auxiliary indicators will be blood pressure load values and salt sensitivity risk rate. The exploratory indicator will be acupoint diagnosis. The safety evaluation indicator will be incidence of adverse events.

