#### Diagnostic criteria of western medicine

3.2.1

The diagnosis criteria of essential hypertension will be in accordance with the 2018 revision of the guidelines for prevention and treatment of hypertension of China, revised by the China hypertension Revision Commission.^[4]^ Without antihypertensive drugs, hypertension will diagnosed when systolic blood pressure (SBP) of clinic blood pressure (CBP) ≥140 mmHg and/or diastolic blood pressure (DBP) of CBP ≥90 mmHg are measured 3 times (not on the same day). The patients who had the history of hypertension and were taking antihypertensive drugs will also be diagnosed with hypertension. The diagnostic criteria of ambulatory blood pressure monitoring (ABPM) for hypertension are: 24 hour average SBP/DBP ≥130/80 mmHg; daytime SBP/DBP ≥135/85 mmHg; nighttime SBP/DBP ≥120/70 mmHg. The diagnostic criteria of home blood pressure monitoring (HBPM) ≥135/85 mmHg, which corresponded to 140/90 mmHg in CBP.

According to whether participants has cardiovascular risk, including target organ damage, cardiovascular risk factors, diabetes, and clinical complications, they will divided into 4 levels: low risk (without risk factors), medium risk (with 1–2 risk factors), high risk (with ≥3 risk factors), very high risk (with target organ damage, chronic kidney disease stage 3, or diabetes).

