## Statistical analysis

9

SPSS 20.0 statistical software will be used for data statistics (SPSS Inc, Chicago, IL). The frequency percentage will be used to describe the demographic data. For the measurement data with normal distribution and homogeneous variance, mean ± standard deviation (\bar{x} (Latex code) ± s) will used to describe the data. Paired and independent sample *t* test will used for intragroup and intergroup comparison respectively. For the measurement data of non-normal distribution, nonparametric test will be used. The blood pressure value will be analyzed by repeated measurement analysis of variance. In the correlation analysis of 2 theoretically related continuous variables, Pearson correlation coefficient model will be used if the data meet the normal distribution, and Spearman correlation coefficient model will be used if the data are nonnormal distribution. *χ*^2^ test will be used for counting data. All tests will be bilateral; *P* < .05 means the difference is statistically significant. In the correlation analysis, 0 < R≤0.2 means that there is no correlation between variables; 0.2<R≤0.4 means that there is a low correlation between variables; 0.4<R≤0.8 means that there is a moderate correlation between variables; 0.8 < R≤1 means that there is a high correlation between variables.

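### The primary outcome is not reduced to one pressure variable, one visit or one deciding test, while P < .05 applies to every test, so the plan does not hold the primary false-positive rate at 5%

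*Protocol article*

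**What the plan says.** The abstract (Methods) states: "The primary outcome will be 24-hour ambulatory blood pressure". Section 6.1 (Main outcome) gives the device, the arm, the recording length and a validity rule, "There are at least 20 daytime blood pressure readings and 6 nighttime blood pressure readings". It then gives the schedule: "Ambulatory blood pressure monitoring will be evaluated in the first week (baseline period), the fifth week (after acupuncture period), and the seventh week". Neither place says systolic or diastolic, or which of weeks 5 and 7 decides.

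Section 3.2.1 shows that ambulatory monitoring yields several distinct means: "24 hour average SBP/DBP ≥130/80 mmHg; daytime SBP/DBP ≥135/85 mmHg; nighttime SBP/DBP ≥120/70 mmHg". These are diagnostic thresholds, not endpoints.

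Section 9 (Statistical analysis) has a sentence specific to blood pressure: "The blood pressure value will be analyzed by repeated measurement analysis of variance". For normally distributed measurement data in general it lists paired and independent t tests: "test will used for intragroup and intergroup comparison respectively". On significance it says "All tests will be bilateral", and that P < .05 "means the difference is statistically significant". It names no primary comparison and no order of testing.

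**The concern.** A 24-hour recording gives at least two numbers, a systolic and a diastolic mean, and there are two post-treatment visits. Repeated-measures ANOVA can combine the visits in one model, but it is run once per pressure variable. It also returns group, time and group-by-time effects, and the document does not say which one answers the primary question. The t-test sentence leaves comparisons at each visit open as well.

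Two things are at stake. First, under one uniform P < .05 rule, the chance of at least one false primary finding exceeds 5% if more than one of these results can be claimed. Second, a reader of the final report could not tell a result chosen in advance from one picked afterwards. The sample size in section 4.2 (22.57, rounded to 23 per arm) also rests on a variable that is not named.

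**Working it through.** **The plan's own figures.** The document states no overall error rate; its only error figure is P < .05 per test. The 22.57 per arm cannot be reproduced, because the article gives no margin, SD, alpha or power. The dropout step can: 23 × 1.2 = 27.6, so 28 per arm and 56 in total. Only the 23 per arm is used below.

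**Inputs from the document.** 23 per arm (section 4.2); visits at weeks 1, 5 and 7 (section 6.1); two-sided 0.05 per test (section 9).

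**Assumed inputs (not in the document).** No treatment effect on any measure. Correlation between systolic and diastolic 0.6 to 0.8; between visits 0.5 to 0.8. Where daytime and nighttime means are added: 24-hour with daytime 0.95, 24-hour with nighttime 0.8, daytime with nighttime 0.65. One significant result counts as a positive primary.

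**Step 1: ceiling under independence.** For k independent tests the chance of at least one false positive is 1 − 0.95^k.
- k = 2: 1 − 0.95² = 9.75%
- k = 4: 1 − 0.95⁴ = 18.5%
- k = 12: 1 − 0.95¹² = 46.0%

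Ambulatory pressures in the same patients are strongly correlated, so these are too high.

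**Step 2: correlated tests.** Simulation of 20,000 trials per setting, 23 per arm and three visits, with equal correlation between visits. The lower rate in each row comes from the highest correlations.

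| Reading of the plan | Tests | Chance of at least one false positive | Multiple of 5% |
|---|---|---|---|
| One named variable, one named test | 1 | 5% | 1 |
| 24-hour SBP and DBP, one ANOVA group-by-time test each | 2 | 7.9% to 8.9% | 1.6 to 1.8 |
| 24-hour SBP and DBP, t test at weeks 5 and 7 | 4 | 11.8% to 15.5% | 2.4 to 3.1 |
| Six means, one ANOVA group-by-time test each | 6 | 14.3% to 16.5% | 2.9 to 3.3 |
| Six means, t test at weeks 5 and 7 | 12 | 21.2% to 27.2% | 4.2 to 5.4 |

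The six means are the 24-hour, daytime and nighttime SBP and DBP.

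**Step 3: cross-check.** Drawing correlated normal test statistics directly (300,000 draws per setting) gives 12.0% to 15.6% for the four visit-wise tests and 21.1% to 27.1% for the twelve, in agreement with the table. Two tests correlated at 0.6 to 0.8 give 7.8% to 8.8%, close to the ANOVA row.

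**Step 4: after a fix.** One named variable with one named test returns the rate to 5%. If four tests were kept as alternative primaries with a Bonferroni limit of 0.05/4 = 0.0125 each, the overall rate would be 3.3% to 4.4%.

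**The case against.** The strongest reply is that section 9 assigns blood pressure to repeated-measures ANOVA, which can take all three visits in one model. That stands. The smallest family is therefore two tests, not four, and the smallest inflation is 1.6 to 1.8 times the nominal rate. It does not settle the matter: systolic or diastolic stays open, the deciding effect is not named, and the t-test sentence still permits visit-wise comparisons.

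A reader might also infer twelve primary tests, from six means at two visits. The document does not support this. Daytime and nighttime values appear as diagnostic thresholds in 3.2.1, as part of the definition of blood pressure load (an auxiliary outcome) in 6.3, and as minimum reading counts in 6.1. None is listed as a primary endpoint. Rates above the 21-27% range would need correlations too low for means that overlap: the 24-hour mean contains the daytime and nighttime readings.

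Nor does the article state that any one significant result makes the primary outcome positive. P < .05 is given as a convention for each test. The rates above apply only if that reading is taken, which nothing in the text prevents.

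Section 4.2 frames the purpose as non-inferiority, while the rates here are for two-sided tests of a difference, as section 9 describes. They are not error rates for a non-inferiority claim.

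Finally, multiplicity procedures are commonly left to a full protocol or SAP, and neither is shown. The absence of such a procedure from an article is not the point. Which variable and visit are primary is the definition of the trial's main question, which is what section 6.1 sets out to give, and the uniform P < .05 rule is stated text.

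**Conclusion.** The concern holds in a limited form. The primary outcome is not fixed to one variable, one visit or one deciding test, and the stated significance rule applies equally to all of them, so following the article does not hold the primary false-positive rate at 5%. If any significant 24-hour systolic or diastolic result may be claimed, the rate is about 8-9% under the method named for blood pressure and about 12-16% under visit-wise t tests. The 21-27% range needs an extension to daytime and nighttime means that the document does not make. The sizes rest on the assumed correlations; the direction does not. This should be changed. It is a defect in the definition of the main question, and the trial can still be analysed properly once that definition is given.

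**What to change.** In section 6.1, state one primary variable and one deciding visit. An example is 24-hour mean systolic pressure at week 5, which is the end of treatment; another single choice made in advance would cure the defect equally well. In section 9, name the single between-group test that decides it, at two-sided 0.05. If the repeated-measures model is kept for this purpose, say which effect or contrast is decisive. Make the 24-hour diastolic mean, the daytime and nighttime means and all week-7 values secondary, either tested in a fixed order or reported with confidence intervals only.

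The cost is one sentence in each section and an update of the registry entry where it differs. No additional patients or measurements are needed. The downside is that success on another ambulatory measure can no longer be called primary.
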